## Abstract

**Background:**

The epiretinal membrane (ERM) is a degenerative condition associated with age, which can cause loss of vision and/or metamorphopsia. The treatment of symptomatic ERM involves surgical removal including a vitrectomy followed by peeling of the ERM using a microforceps. As the internal limiting membrane (ILM) is adherent to the ERM, it is sometimes removed with it (spontaneous peeling). If ILM remains in place, it can be removed to reduce ERM recurrence. However, it is important to clarify the safety of ILM peeling, while it increases surgical risks and cause histological disorganization of the retina that can lead to microscotomas, may be responsible for definitive visual discomfort.

**Methods:**

PEELING is a prospective, randomized, controlled, single-blind, and multicentered trial with two parallel arms. This study investigates the benefit/risk ratio of active ILM peeling among individuals undergoing ERM surgery without spontaneous ILM peeling. Randomization is done in the operating room after ERM removal if ILM remains in place. After randomization, the two groups—“active peeling of the ILM” and “no peeling of the ILM”—are compared during a total of three follow-up visits scheduled at month 1, month 6, and month 12. Primary endpoint is the difference in microscotomas before surgery and 6 months after surgery. Patients with spontaneous peeling are not randomized and are included in the ancillary study with the same follow-up visits and the same examinations as the principal study.

Relevant inclusion criteria involve individuals aged > 18 years living with idiopathic symptomatic ERM, including pseudophakic patients with transparent posterior capsule or open capsule or lensed patients with age-related cataracts. The calculated sample size corresponds to 53 randomized eyes (one eye/patient) per arm that means 106 randomized eyes (106 randomized patients) in total and a maximum of 222 included patients (116 spontaneous peeling).

**Discussion:**

ILM peeling is often practiced in ERM surgery to reduce ERM recurrence. It does not impair postoperative visual acuity, but it increases the surgical risks and causes anatomical damages. If active ILM peeling is significantly associated with more microscotomas, it may contraindicate the ILM peeling during primitive idiopathic ERM surgery.

**Trial registration:**

ClinicalTrials.gov, NCT02146144. Registered on 22 May 2014. Recruitment is still ongoing.

## Administrative information

Note: the numbers in curly brackets in this protocol refer to SPIRIT checklist item numbers. The order of the items has been modified to group similar items (see http://www.equator-network.org/reporting-guidelines/spirit-2013-statement-defining-standard-protocol-items-for-clinical-trials/).

## Introduction

### Background and rationale {6a}

The epiretinal membrane (ERM) is a degenerative condition associated with age, characterized by a fibrocellular proliferation developing at the surface of the macula. The treatment of symptomatic ERM remains surgical removal including a vitrectomy followed by peeling of the ERM using a microforceps. As the internal limiting membrane (ILM) is adherent to the ERM, it is sometimes removed with it (spontaneous peeling). If it remains in place, the relevance of ILM intentional removal (“active peeling”) remains controversial.

The surgeons often peel the ILM as an adjuvant action expected to increase the success rate of the surgery. Some observational studies found that the risk of recurrence is reduced from 7%–23% without ILM peeling to 0%–4% with ILM peeling during idiopathic ERM removal [1–6]. In a meta-analysis, Azuma et al. [7] found a significant reduction of recurrence rate in case of ILM peeling during idiopathic ERM surgery (odds ratio 0.25; 95% confidence interval 0.12–0.49). Two randomized clinical trials compared ILM peeling or not: De Novelli et al. found a similar difference after 6 months (4% of recurrence with ILM peeling and 17% without) but did not reach significance; Tranos et al. did not found any recurrence in both groups after 12 months [8]. In case of recurrent ERM, vision is impaired in only half of the patients; if visual loss does occur, a second ERM surgery is possible [9].

The peeling of the ILM does not alter nor improve postoperative visual acuity (VA) [7–11]. This additional procedure lengthens the operation, increases the surgical risks (phototraumatism, retinal tear, central or eccentric macular hole) [12–14] and the risk of histological disorganization of the retina [15], which can result in one or more microscotomas with possible definitive visual discomfort for the patients. ILM is formed by Muller cells end-feet and ILM peeling results in significant damage of Muller cells [16]. Swelling of the arcuate fiber layer (SANFL) [17] and dissociated optic nerve fiber layer (DONFL) [18, 19] are well-described retinal changes due to ILM peeling but no impairment of VA has been linked to these findings.

Thanks to microperimetry, it is now possible to study more precisely the functional impairment in various retinal pathologies [20], especially with optical coherence tomography (OCT) scanning laser ophthalmoscope (SLO) microperimetry which couples microperimetry data with OCT data [21]. A retrospective study using microperimetry by Tadayoni et al. found that ILM peeling may reduce retinal sensitivity and significantly increase the incidence of microscotomas after macular surgery [22]. These abnormalities may explain the visual discomfort reported by some patients undergoing ERM and are not detected by measurement of VA and/or visual field. In a retrospective study, Deltour et al. found that active peeling was associated with more numerous and deeper microscotomas than spontaneous peeling [23]. Their localization seemed to fit the gripping areas of the ERM and ILM.

The purpose of this study is to clarify the benefit/risks ratio of the ILM peeling during ERM surgery. Microperimetry takes a central role to search for the number and type of microscotomas induced by the surgery. This study also further refines the analysis of anatomical abnormalities visualized by spectral domain optical coherence tomography (SD-OCT) and their correlation with the visual outcome of this surgery and the presence of microscotomas.

If active ILM peeling is significantly associated with more microscotomas, it may contraindicate the ILM peeling during primitive idiopathic ERM surgery.

### Objectives {7}

The main objective is to compare differences in microscotomas between the “active peeling of the ILM” group and the “no ILM peeling” group between the inclusion visit and 6 months after surgery. The main criterion is the difference between the number of microscotomas (sensitivity < 10 dB).

The secondary objectives are the difference of anatomical and functional changes of the retina between the two groups at 1, 6, and 12 months and the rate of recurrence of ERM at 12 months. Various endpoints are assessed: VA measurements (ETDRS scale) and near vision (Parinaud); microperimetry; questionnaires of visual discomfort; and SD-OCT analysis.

An ancillary study is also conducted and concerns the patients who undergo spontaneous peeling of the ILM during the surgery, as they cannot be included in the main study. The aim is to compare primary and secondary endpoints between patients with spontaneous peeling and patients in the active peeling group at inclusion visit and 1, 6, and 12 months after surgery.

### Trial design {8}

PEELING is a two-arm prospective, multicentered, controlled, randomized, and single-blind trial associated with an ancillary study about patients with spontaneous ILM peeling.

## Methods: participants, interventions, and outcomes

### Study setting {9}

This study is multicentered and national; patients are recruited in the six national ophthalmology services of the Nantes University Hospital, of the Lariboisière Hospital, of the Dijon University Hospital, of the Fondation Ophtalmologique Adolphe de Rothschild, of the private hospital of Saint-Herblain (Polyclinique de l’Atlantique), and of the Sourdille private hospital of Nantes.

As stated before, the recruitment is scheduled on six hospitals centers.

### Eligibility criteria {10}

The patients experiencing ERM are usually aged > 60 years. The etiology is mostly idiopathic but can be secondary to various diseases (diabetic retinopathy, inflammation [uveitis], trauma, recent eye surgery, retinal detachment or tear). Idiopathic ERM affect about 7% of patients after the age of 50 years according to the Blue Mountains Eye Study (conducted on an Australian population) [24]. They are often asymptomatic and not treated. In this study, 28% of patients had a loss of VA and 7.1% had metamorphopsia (distortion of lines) [24]. They then needed surgery.

The study population concerns only patients with symptomatic idiopathic ERM, responsible for symptoms such as decreased VA and metamorphopsia.

Other inclusion criteria are patients aged ≥ 18 years and women without childbearing potential or with active contraception (intrauterine device, contraceptive pill, or contraceptive implant). For patients with both eyes affected, the treated eye in the protocol is the one that is the most severely affected.

For the patients with preoperative lens opalescence, a cataract surgery is performed. As ERM mainly affects patients aged > 60 years, most of them already have preoperative bilateral lens opalescence. The worsening of the cataract in the year after vitrectomy is the most common surgery complication of ERM. The onset or continued worsening of postoperative cataracts may alter visual recovery and disrupt the assessment of visual function including retinal sensitivity microperimetry [25–27]. Furthermore, combined cataract surgery and vitrectomy for ERM is a commonly used technique that provides good functional results [28].

The main non-inclusion criteria are the presence of another pathology: age-related macular degeneration; retinal vein occlusion; diabetic retinopathy; glaucoma with macular visual field defect; or uveitis. Patients who underwent any recent eye injuries or eye surgeries (> 6 months) are also excluded. All the inclusion and non-inclusion criteria are in the Table 1.

**Table 1 Tab1:** Inclusion and non-inclusion criteria

Inclusion criteria	Non-inclusion criteria
✓ Adult patients (aged > 18 years), woman without childbearing potential or active contraception (intrauterine device, contraceptive pill, or contraceptive implant)	✓ Patient with other retinal pathologies such as age-related macular degeneration (“AMD”), retinal vein occlusion, diabetic retinopathy, glaucoma with macular visual field defect
✓ Patients with an idiopathic symptomatic epimacular membrane; for patients with both eyes affected, the treated eye in the protocol will be the one that is most severely affected	✓ Patients with uveitis or a history of uveitis
✓ Pseudophakic patients with transparent posterior capsule or open capsule or lensed patients with age-related cataracts	✓ Patients with any recent eye injuries or eye surgeries (< 6 months)
✓ Patients with social security	✓ Patients participating in interventional clinical trial
✓ Patients able to understand and follow the trial instructions	✓ Pregnant or breastfeeding women
✓ Patients who have signed an informed consent	✓ Vulnerable people: persons deprived of liberty, under trusteeship, or under curatorship

### Who will take informed consent {26a}

Patient’s written consent was obtained by the investigator before any study-specific procedures. Participation is voluntary, individuals may withdraw at any stage, and participation does not affect the treatment of the individual.

### Additional consent provisions for collections and use of participant data and biological specimens {26b}

Not applicable as no biological specimens were collected as part of this trial.

### Interventions

#### Explanation for the choice of comparators {6b}

The main comparator is microperimetry. It is justified by the fact that no study has shown that ILM peeling modifies postoperative VA but many studies have demonstrated anatomical damages. Visual outcome is not limited to VA. Microperimetry, a more refined test, can show microscotomas. These microscotomas do not impair VA but can cause permanent visual discomfort. Deltour et al. [23] showed in a retrospective study that active ILM peeling is associated with more microscotomas than spontaneous peeling. This preliminary result has to be verified by a prospective randomized clinical trial.

#### Interventions description {11a}

As shown in the study diagram (Fig. 1), the screening visit is conducted between day 90 and day 7 (D-90 to D-7) before surgery. It consists of an evaluation of the eye, VA and near vision, and SD-OCT analysis.

**Fig. 1 Fig1:**
[figure not shown]
Study diagram

On the day of the surgery (D-0), for phakic eyes with cataract, phacoemulsification is performed. For all patients, central and peripheral vitrectomy (25 gauge) and dissection of the ERM are performed. Membraneblue-Dual® is used to stain ILM for an exposure time of 1 min. Intraoperative pictures are then taken to see the possible spontaneous ILM peeling: if ILM remains, the patient is randomized in the operating room in the “no peeling” group or in the “active peeling” group. In the “active peeling” group, the ILM peeling is performed on at least two papillary diameters around the fovea, which corresponds to a “circle” of four papillary diameters.

At the end of the surgery, the retinal periphery is checked. The operation is filmed and the anonymous videos are centralized in Nantes to compare the appearance of microscotomas and grip areas of the ERM and ILM seen by video and photo. For about 30% of patients [29], the ILM is spontaneously peeled off. These patients are not randomized but they can be included, if they want it, in the ancillary study. This ancillary study has the same follow-up visits (at 1, 6, and 12 months) with the same examinations as the principal study.

A total of three follow-up visits are planned over a time span of 12 months postoperatively (at 1, 6, and 12 months). At each visit, the following are performed: VA on the ETDRS scale; near vision (Parinaud scale); SD-OCT; microscopic examination of the eye; microperimetry; fundus photography and postoperative “Patient discomfort” questionnaire; biomicroscopic examination of the anterior segment; retinal photography; and an assessment of adverse events (AE). The schedule of the trial is shown in Table 2. To avoid any bias, the follow-up visits are made by masked ophthalmologists and orthoptists who do not know if ILM was actively peeled off.

**Table 2 Tab2:** Study schedule

Actions	Inclusion visit D-90 and D-7	D0 (Surgery)	M1 (30days±7days starting D0)	M6 (6 months ± 15 days starting D0)	M12 (12 months ± 15 days starting D0) End of study
Patient information	X				
Informed consent	X				
History (medications taken…)	X				
Randomization		X			
Surgery		X			
ETDRS visual acuity score and near vision (Parinaud)	X		X	X	X
Evaluation of the appearance of the lens at the slit lamp	X				
Biomicroscopic examination of the anterior segment	X		X	X	X
Fundus	X		X	X	X
SD OCT	X		X	X	X
OCT/SLO: microperimetry	X		X	X	X
Retinal photography	X		X	X	X
“Patient discomfort” questionnaire	X		X	X	X
Adverse events		X	X	X	X
2 Photographs		X			
Video		X			

#### Criteria for discontinuing or modifying allocated interventions {11b}

The research could be discontinued as a result of the patient withdrawing their consent. The sponsor reserves the right to discontinue the study at any time for reasons that are well documented, especially in the case of unexpected AEs that compromise the safety of patients included in this study.

Finally, if the recruitment rate is too low or in cases of non-compliance with Good Clinical Practice, the study may also be stopped prematurely.

#### Strategies to improve adherence to interventions {11c}

This is a surgical procedure so patient adherence is not applicable.

#### Relevant concomitant care permitted or prohibited during the trial {11d}

Implementing “not-peeling” or “peeling” will not require alteration to usual care pathways (including use of any medication) and these will continue for both trial arms. In the postoperative phase, the standard treatment is a combination steroid and antibiotic eye drops (one drop three times per day) for the duration of 1 month.

#### Provisions for post-trial care {30}

At the end of the clinical research, the patient will be followed by their opthalmologist and will benefit from the usual care of their disease.

The sponsor takes out an insurance policy covering the financial consequences of its civil liability in compliance with the regulations.

#### Outcomes {12}

The main endpoint is the difference between the number of microscotomas (sensitivity < 10 dB) found before surgery and the number of microscotomas found at 6 months (number in the range of 0–29).

The secondary endpoints are:
VA measured on the ETDRS scale and near vision (Parinaud) (at inclusion visit and 1, 6, and 12 months after surgery)Number and types of microscotomas by microperimetry (before and after surgery)Mean retinal sensitivity by microperimetry before and after surgery (at 1, 6, and 12 months)Patient visual discomfort questionnaire: symptoms and subjective improvement before and after surgery (at 1, 6, and 12 months)Incidence of changes of the retinal nerve fiber layer SD by OCT analysis (B scan and C scan) before and after surgerySinusoid (IS/OS) line disruption by OCT analysis (B scan and C scan) before and after surgeryMean retinal thickness by OCT analysis (B scan) before and after surgeryRetinal nerve fiber layer thickness by OCT analysis (B scan) before and after surgeryOuter segment photoreceptor thickness by OCT analysis (B scan) before and after surgeryRecurrence of ERM by OCT analysis (B scan and C Scan)Operative report and the video recording area of ERM and ILM gripping (study of the correlation with the microscotoma(s).

The endpoints of the ancillary studies are:
The main criterion: the difference between the number of microscotomas (sensitivity < 10 dB) found before surgery and the number of microscotomas found at 6 months (number in the range of 0–29).VA measured on the ETDRS scale and near vision (Parinaud) (at inclusion visit and 1, 6, and 12 months after surgery)Number and types of microscotomas by microperimetry (before and after surgery)Mean retinal sensitivity by microperimetry before and after surgery (at 1, 6, and 12 months)Patient visual discomfort questionnaire: symptoms and subjective improvement before and after surgery (at 1, 6, and 12 months)Incidence of changes of the retinal nerve fiber layer SD by OCT analysis (B scan and C scan) before and after surgerySinusoid (IS/OS) line disruption by OCT analysis (B scan and C scan) before and after surgeryMean retinal thickness by OCT analysis (B scan) before and after surgeryRetinal nerve fiber layer thickness by OCT analysis (B scan) before and after surgeryOuter segment photoreceptor thickness by OCT analysis (B scan) before and after surgeryRecurrence of ERM by OCT analysis (B scan and C scan)

#### Participant timeline {13}

The treatment duration per patient corresponds to the surgery (1 day), the patient’s follow-up to 12 months and the recruitment period to 72 months.

#### Sample size {14}

A retrospective study conducted in the Department of Ophthalmology of the University Hospital of Nantes in 2013 [23] showed that of 11 patients who received active peeling, the number of microscotomas was 2.5 ± 3.1 preoperatively and 6.5 ± 7.3 at 1 month.

Based on the number of microscotomas found in the active peeling group in our retrospective study, with 80% power and a type I error of 5%, 100 patients are needed to highlight a halving of the number of microscotomas in the non-peeling group relative to the active peeling group (i.e. 6 ± 6 microscotomas average peeling in the active group compared to 3 ± 4.6 in the non-peeling group).

Usually, only very few patients do not attend their 6-month visit. However, the occurrence of EIGs (endophthalmitis, retinal detachment) may prevent the determination of the number of microscotomas at 6 months by microperimetry. Assuming that at most 5% of patients will be affected, 106 patients will be randomized, or 53 patients per group.

As all the patients with spontaneous peeling during surgery will not be randomized, > 106 have to be enrolled. The estimated number of spontaneous peeling was initially 30% [23], so the number of patients enrolled were thought to be 156. During the study, we noted that spontaneous peeling occurred in 50.2% of cases and so the number of patients to enroll in the study has been revised to 222 patients (amendment to the protocol in December 2017).

The ability of the six centers to recruit is estimated to be 120 patients per year (30 patients per center), given that the primitive ERM is a common disease.

#### Recruitment {15}

Recruitment is planned over a period of 72 months. Symptomatic idiopathic ERM is a common pathology found in each center at the rate of five cases per center per month, making these recruitment targets achievable.

### Assignment of interventions: allocation

#### Sequence generation {16a}

Randomization will be conducted openly and stratified by center. It will be performed according to a 1:1 ratio and balanced by blocks. The software used for the randomization is SAS version 9.4.

#### Concealment mechanisms {16b}

The random numbers will be generated by computer. Participants are randomized into blocks as the allocation progresses, a block being a subgroup of predetermined size within which there is a random allocation of patients.

#### Implementation {16c}

The randomization key is known only to the biostatistician and the data managers, to make it impossible for the investigator to assign a particular treatment.

During the surgery, if no spontaneous ILM peeling occurs, the patient is randomized at the block.

Patients are randomized into two groups
Group 1: “no peeling” where the ILM peeling will not be madeGroup 2: “active peeling” where the ILM peeling is performed

### Assignment of interventions: blinding

#### Who will be blinded {17a}

The randomization is done during the surgery. To comply with the simple blind, the surgical team should not discuss the surgical procedure chosen in the operating block (so that the patient cannot hear).

Furthermore, to avoid any bias, the follow-up visits will be made by ophthalmologists and orthoptists who will not know what action has been carried out (masked team).

#### Procedure for unblinding if needed {17b}

To maintain the single blinding, the operative report will mention that the surgery was done following the protocol defined in the PEELING study. At the end of the study, patients will be informed of the results.

### Data collection and management

#### Plans for assessment and collections of outcomes: description of the parameters for evaluating efficacy {18a}

Here are detailed the parameters to assess effectiveness:

First, the microperimetry is a non-invasive test that allows a real-time, qualitative, and quantitative assessment of visual function. Microperimetry is introduced in routine clinical diagnostic procedure which, with extreme precision, defines the retinal attachment point and the threshold of differential sensitivity of the retina. Retinal sensitivity is better within 3° around the fixing point, with a mean foveal threshold of 20 dB, and a 0.275 dB mean decrement for each 10°. Scotomas are defined as absolute (if the patient does not perceive the maximum stimulation, the sensitivity is 0 dB) or relative (reduction of retinal sensitivity compared to normal values is < 10 dB). Assessing retinal function with this tool provides valuable clinical and pathophysiological information. These abnormalities could explain the hitherto non-assessable visual discomfort by conventional methods reported by some patients undergoing epiretinal membrane or macular hole surgery.

For all patients and to standardize the measurement, we use the “Ivana” protocol directed by the ophthalmology service of Lariboisière: a fixation target consisting of a red cross 2° in diameter, a white background monochromatic 4 asb, stimulus size Goldmann II with a projection time of 200 ms and a grid of 29 measurement points in the central 9° (centered on the fovea) with a 4–2-1 “double staircase” threshold strategy. Automatic “eye-tracking” will record eye movements throughout the exam. In addition, we will conduct topographies of the macular area in spectral OCT/SLO combined with microperimetry (OPKO/OTI, Miami, FL, USA).

Second, the scale of evaluation of the ETDRS VA will be performed by a masked orthoptist so as not to influence the patient’s response.

Third, a “Patient discomfort” questionnaire made by the ophthalmologist team will be given to the patient to evaluate their symptoms before and after the surgery.

Fourth, the SD-OCT will allow a precise anatomical pre- and postoperative analysis of the macula. The projected sequences include:
RASTER (B scan): 1024 A scans; 25 sections (nine frames) spaced by 240 μm, covering an area of 20° × 20°FRONTAL acquisition (C scan): 512 A scans; 193 sections (16 frames) spaced by 30 μm, covering an area of 20° × 20°.

On these sections, we will study:
The retinal thickness at 1000 μm central and the fovean crown at 3000 μm as well as the total macular volumeThe presence of intra-retinal and/or subretinal edemaAt the fovea level: analysis of internal trunk segments/outer segments of photoreceptors, integrity of the external limiting membrane, thickness of the layer of the outer section of the photoreceptors,In regard to microscotomas: thickness of the layer of ganglion cells at different timesThe rate of anatomical abnormalities that are detectable from the layer of optical fibers in frontal “DONFL” and “SANFL”The ERM rate of recurrence

Finally, the pre- and postoperative videos and photographs will be analyzed. The ERM peeling procedure with or without ILM is filmed. A photo or screen shot of the video just after staining with Membraneblue-Dual® and a photo or a video screen shot at the end of ILM peeling will be made (depending on the blocks, certain devices enable video only videos while others are able to take both videos and photos).

The objective of the first picture is to visualize the spontaneous ILM peeling and scope. The purpose of the second photo is to see the surface of active ILM peeling. The advantage of video is that the gripping zone of the ERM and ILM can be viewed.

Anonymous pre- and postoperative photos (according to the code defined in section 6.1.2.) will be sent to central Nantes and examined by an ophthalmologist from Nantes to see the gripping areas of the ERM and ILM.

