#### Methods for additional analyses (e.g. subgroup analyses) {20b}

Analyses for the ancillary study. The patients with spontaneous peeling are not randomized and are compared to the “active peeling” group.

The main criterion is, like in the main study, the difference between the number of microscotomas (sensitivity < 10 dB) found before surgery and the number of microscotomas found at 6 months (number in the range of 0–29). The other endpoints are the same as the secondary endpoints of the main study, without the analysis of the video recording.

Mixed linear regressions models and stratified Chi-square test are used for comparisons.

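### The relative-scotoma definition in section {18a} contradicts the < 10 dB sensitivity threshold of the endpoint and leaves microscotomas of 1–9 dB without a type

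*Protocol article*

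**What the plan says.** Three sections of the protocol article give the counted event a threshold, and they agree.

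- Objectives {7}: "The main criterion is the difference between the number of microscotomas (sensitivity < 10 dB".
- Outcomes {12}: "The main endpoint is the difference between the number of microscotomas (sensitivity < 10 dB) found before surgery". The main criterion of the ancillary study is listed there with the same threshold.
- Methods for additional analyses {20b}, for the ancillary comparison: "the difference between the number of microscotomas (sensitivity < 10 dB) found before surgery and the number of microscotomas found at 6 months".

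Statistical methods {20a} restates the primary endpoint without a dB value.

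The section on assessment of outcomes {18a} describes microperimetry and sorts scotomas into two types. The first is "absolute (if the patient does not perceive the maximum stimulation, the sensitivity is 0 dB". The second is "relative (reduction of retinal sensitivity compared to normal values is < 10 dB". The same paragraph gives the normal reference, "with a mean foveal threshold of 20 dB, and a 0.275 dB mean decrement for each 10" degrees, and the next paragraph gives the test pattern, "a grid of 29 measurement points in the central 9° (centered on the fovea".

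Types matter to the analysis. Outcomes {12} lists the number and type of microscotomas as a secondary endpoint of both the main and the ancillary study, and {20a} plans to describe and compare the type before surgery and at 1, 6 and 12 months.

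**The concern.** The endpoint sections set a ceiling on the sensitivity that remains at a point. Section {18a} sets a ceiling on the sensitivity that has been lost. When normal is about twice the cut-off, these pick out different points: a small loss leaves a high sensitivity.

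The direct stake is the secondary endpoint on types. A type classification should divide the counted microscotomas into parts that add up to the total. Taken as written, {18a} does not: a moderately deep defect is counted as a microscotoma but has no type, while a shallow one has a type but is not counted.

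There is a conditional stake for the primary endpoint. Section {18a} introduces itself as the detail on the effectiveness parameters, and nothing in the article says how its types relate to the < 10 dB count. If someone tallied absolute plus relative scotomas by the {18a} wording, a point whose loss deepened from 5 to 15 dB would drop out of the tally.

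**Working it through.** **Inputs.** Endpoint threshold: sensitivity < 10 dB ({7}, {12}, {20b}). Absolute: 0 dB ({18a}). Relative: reduction from normal < 10 dB ({18a}). Normal reference: 20 dB ({18a}). Grid: 29 points ({18a}).

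**The plan's own sample size, for reference.** Sample size {14} plans on 6 ± 6 versus 3 ± 4.6, 80% power and 5% type I error (two-sided assumed).

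- Pooled SD = √((6² + 4.6²)/2) = √28.58 = 5.346.
- n per arm = 2 × (1.960 + 0.842)² × 28.58 / 3² = 49.9, so 50 per arm and 100 in total.
- Allowing for 5% not evaluable: 100/0.95 = 105.3, so 106.

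Both stated figures reproduce. Neither uses the {18a} definition, so nothing in the sample size changes.

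**The two definitions, in whole dB from 0 to 20.** Let s be the sensitivity at a point; the reduction is 20 − s.

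| s (dB) | Reduction (dB) | Counted by the endpoint (s < 10) | Type under {18a}, literally |
|---|---|---|---|
| 0 | 20 | yes | absolute |
| 1–9 | 19–11 | yes | none |
| 10 | 10 | no | none |
| 11–19 | 9–1 | no | relative |
| 20 | 0 | no | none |

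The endpoint set is 0–9 dB. The {18a} set is 0 dB plus 11–19 dB. The overlap is 0 dB alone. Two examples: at 15 dB the reduction is 20 − 15 = 5, so the point is a relative scotoma but not a microscotoma; at 5 dB the reduction is 20 − 5 = 15, so it is a microscotoma but not a relative scotoma.

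**Does the result depend on using 20 dB?** Hardly. At the stated decrement of 0.275 dB per 10°, a point 4.5° from the fovea (taking 9° as the diameter of the grid) loses 0.275 × 4.5/10 = 0.12 dB. Even if the decrement were per 1°, the loss would be 0.275 × 4.5 = 1.24 dB. With normal at 19 dB the literal set is 0 and 10–18 dB; at 18 dB it is 0 and 9–17 dB. The overlap then grows by one value at most (9 dB), and 1–8 dB still have no type.

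**Would reversing the inequality repair it?** A reduction of more than 10 dB from 20 dB means s < 10, which is 0–9 dB and matches the endpoint. But with normal at 19 dB it gives 0–8 dB, and at 18 dB it gives 0–7 dB. A rule stated directly on sensitivity does not move with the reference value.

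**Illustration of a literal tally (assumed values, one visit).** Assume normal 20 dB, between-eye SD 2 dB, within-eye SD 3 dB and values rounded to whole dB. The SD at a point is √(2² + 3²) = 3.61.

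- Eye mean 12 dB: the endpoint count is 29 × P(s < 9.5) = 29 × Φ(−0.69) ≈ 7; the {18a} count is 29 × P(10.5 < s < 19.5) ≈ 19.
- Eye mean 14 dB: the endpoint count is 29 × Φ(−1.25) ≈ 3; the {18a} count is ≈ 22.

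In simulation under the same assumptions, the correlation between the two counts is about −0.95 at 12 dB, −0.81 at 14 dB and −0.11 at 16 dB. It therefore depends strongly on the assumed mean. None of these means or SDs comes from the article.

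**The case against.** A reader might infer that the primary count itself is not fixed, because the trial appears to carry two rival definitions of a microscotoma. The article does not support that. Wherever the endpoint is given a threshold it is the same one, and {20a}, which omits it, adds no conflict. The {18a} sentence sits in a general description of microperimetry. It speaks of scotomas, not microscotomas, and does not mention the endpoint or the count. The standardized examination begins in the following paragraph and contains no such rule.

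The planning figures point the same way. Sample size {14} reports averages of 2.5 before surgery and 6.5 at 1 month, and plans on 6 versus 3. Those are of the order that the < 10 dB rule gives in the illustration above, and far from 19–22. This is suggestive rather than decisive, since the illustration rests on assumed values. The {18a} wording is probably a slip.

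A second tempting inference is that peeling damage would show up as improvement. That requires someone to set aside the repeated endpoint definition and tally by {18a}. Nothing in the article says the count is made that way. The illustration also concerns one visit, while the endpoint is a change compared between arms, so it does not measure bias in the treatment effect. Nor are the definitions wholly opposite: points at 0 dB count under both.

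Finally, {12} and {20a} speak of types without pointing to {18a}, so the link is an inference. It is a strong one, because {18a} gives the only type definitions in the article.

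These arguments limit the point to the type classification and a conditional risk. They do not remove it. The sentence is complete, it is current text, and it is wrong as written. That differs from detail left to a fuller document.

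**Conclusion.** The {18a} definition of a relative scotoma contradicts the < 10 dB sensitivity threshold and has to be reconciled with it. At the stated 20 dB reference the two rules share 0 dB only, and all nine whole-dB values from 1 to 9 that the endpoint counts are left without a type. The secondary endpoint on types, in the main and the ancillary study, therefore has no workable classification as written. This assumes that the types meant are the absolute and relative ones of {18a}.

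The primary endpoint is defined consistently, and the sample size of 100 evaluable and 106 randomized stands. The primary count is exposed only if {18a} is applied as the counting rule, which the article neither prescribes nor expressly excludes. This is a should-fix internal inconsistency.

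**What to change.** Correct the sentence in {18a} so that it follows the endpoint:

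- microscotoma: point sensitivity below 10 dB;
- absolute: 0 dB (maximum stimulus not perceived);
- relative: sensitivity above 0 and below 10 dB.

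Absolute plus relative then equals the primary count for every eye and visit, which also provides a simple data check. Stating the rule on sensitivity is safer than reversing the inequality on the reduction, because it needs no normal value.

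Derive the count and both types by one program from the 29 dB values of each examination, so that every center and visit uses the same rule. Add a few words to {12} or {20a} tying types to these definitions.

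The cost is one corrected sentence, a cross-reference and a derivation check. No new examinations are needed, provided the point-by-point values have been kept. If centers entered only counts or types, ask which rule they applied before the data are analyzed.
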